### 1.10 Study Instrument

There are two study instrument that will be use in this study which are health intervention module and questionnaire.

#### 1.10.1 Development of Health Intervention Module

The health intervention module will be developed in Malay language and validated by the supervisory committee and other expert from Universiti Putra Malaysia (UPM) and Malacca State Health Department. The expert will consist of Public Health specialist and Family Medicine Specialist. Figure 3.4 summarize the flow of health education module development.

[figure not shown]

**Figure 3.4. The schematic diagram for the development of the health education module on increasing willingness for hepatitis C treatment**

The intervention will be delivered during MMT client's appointment with the medical officer in charge of the MMT programs in the form of brief intervention module. The medical officer involve with the study will be brief and undergo training on proper way to conduct questionnaire interview and deliver health education intervention module to the clients. Prior to the intervention session, a baseline assessment will be conducted using validated questionnaire to measure their knowledge regarding hepatitis C, attitude towards hepatitis C infection, subjective norm on hepatitis C treatment, perceived behavioural control on hepatitis C treatment and willingness for hepatitis C treatment. Following that, the brief intervention will be deliver face to face by the medical officer in charge using several materials provided by researcher. The estimated duration of the intervention session is around one and half hours. Table 3.2 summarized the application of TPB constructs in the development of the health education intervention module.

**Table 3.2. Content of Intervention Module based on construct of TPB**

| Construct of theory                                                 | Content                                                                                                                                                                                                                                                                                                           | Method of delivery                                                                                               | Duration and frequency                       |
|---------------------------------------------------------------------|-------------------------------------------------------------------------------------------------------------------------------------------------------------------------------------------------------------------------------------------------------------------------------------------------------------------|------------------------------------------------------------------------------------------------------------------|----------------------------------------------|
| Knowledge regarding hepatitis C
And
Attitude toward behaviour | 
 
• Hepatitis C virus, transmission, sign and symptoms, diagnosis.
 
• Risk of hepatitis C, its complication and relation to cirrhosis and hepatocellular carcinoma
 
• Introduction to DAA treatment and comparing to the old interferon treatment
 
 | Health talk
Video                                                                                             | Content-30 minutes
Discussion –10 minutes |
| Subjective norm on hepatitis C treatment                            | Experience sharing of patient that successfully completed the Hepatitis C treatment using DAA regime                                                                                                                                                                                                              | Recorded video of patient that successfully completed the Hepatitis C treatment using DAA regime and health talk | Content-15 minutes
Discussion –10 minutes |
| Perceived behavioural control on hepatitis C treatment              | The barriers to hepatitis C treatment                                                                                                                                                                                                                                                                             | Recorded video of patient that successfully completed the Hepatitis C treatment using                            | Content-15 minutes
Discussion –10 minutes |

|  |  |                            |  |
|--|--|----------------------------|--|
|  |  | DAA regime and health talk |  |
|--|--|----------------------------|--|

Materials which include health talk and pre-recorded video will be prepared and distribute to the medical officer involve in the study.

### 1.10.2 Questionnaire

Questionnaire that will be use is a self-administered questionnaire that will be distributed to respondent in Malay language. Estimated duration to answer the questionnaire is 20 minutes. The questionnaire section related to knowledge of hepatitis C and construct of TPB will be adopted from previous study. The validity and reliability assessment of the questionnaire will be discussed in respective sections. The set of questionnaires for this study will contain

- i. Section A for Sociodemographic characteristics  
This section will ask regarding respondent sociodemographic characteristics which include age, gender, race, marital status, employment status, monthly income, and education level.
- ii. Section B for MMT treatment profile  
This section will explore regarding history of MMT treatment which include current Methadone dose in mg/day and duration of MMT treatment in years.
- iii. Section C for HIV and Hepatitis C status  
This section will explore regarding respondents HIV and hepatitis C screening history and current HIV and hepatitis C status.
- iv. Section D for history of hepatitis C educational program  
This section will explore regarding respondents' history of attending any hepatitis C educational program.
- v. Section E for substance use history  
This section will explore regarding history of smoking and history of ever and past 6 month injecting and non-injecting drug use as well as alcohol use history among the respondents.
- vi. Section F for willingness for hepatitis C treatment  
This section will explore regarding respondent willingness for hepatitis C treatment is they were diagnosed with hepatitis C and offered for treatment. Respondent will need to select between yes or no to indicate their willingness for hepatitis C treatment.
- vii. Section G for knowledge of hepatitis C  
This section will explore regarding respondent knowledge on hepatitis C infection, transmission, prevention, and treatment. The questionnaire in this section will be adopted from previous study by Arain et al., (2016). Total item in this scale are 19 items. The answer options will be "True", "False" and "Not sure". Each answer will be given 1 mark for "yes" answer and 0 for "no" and "don't know" answer. Total score will range from 0 to 19 and the higher the score reflect higher knowledge of respondent on hepatitis C infection.
- viii. Section H for attitude towards hepatitis C infection and treatment  
This section will explore regarding respondent attitude on hepatitis C infection. The questionnaire in this section will be adopted from previous study (Chen et al., 2013). Total item in this scale are 10 items. For first question of this section, 5-point important scale will be apply in which respondent will need to choose from Not important to very important option. For question 2 until 10, the level of agreement of respondent will be rated using 5-point Likert scale ranging from 1 as "strongly disagree" to 5 as "strongly agree". For this section, the total score will

range from 10 to 50. The higher the score indicate the more positive attitude towards hepatitis C infection.

ix. Section I for subjective norm

This section explores regarding clients perceived social pressure on willingness to hepatitis C treatment. This section will be consist of 4 items and the items will be adopted from guidelines on TPB questionnaire (Francis et al., 2004). The level of agreement of respondent will be rated using 7-point scale ranging from 1 as “strongly disagree” to 7 as “strongly agree”. For this section, the total score will range from 4 to 28. The higher the score indicate the more positive subjective norm on willingness for hepatitis C treatment.

x. Section J for perceived behavioural control

This section explores regarding clients perceived behavioural control on willingness to hepatitis C treatment. It explore on perceived ease or difficulty of performing the behaviour and it is assumed to reflect past experience as well as anticipated impediments and obstacles (Ajzen, 1991). This section will be consist of 4 items and the items will be adopted from guidelines on TPB questionnaire (Francis et al., 2004). The level of agreement of respondent will be rated using 7-point scale ranging from 1 as “strongly disagree” to 7 as “strongly agree”. For this section, the total score will range from 4 to 28. The higher the score indicate the more positive perceived behavioral control on willingness for hepatitis C treatment.

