### Section F: Knowledge on hepatitis C

Please determine whether the following statements hepatitis C infection are true, ~~false~~ or not sure. Please tick (✓) your answer in the space provided.

| No | Statements                                                                            | Answer options |       |          |
|----|---------------------------------------------------------------------------------------|----------------|-------|----------|
|    |                                                                                       | True           | False | Not Sure |
| 1  | Hepatitis C is caused by a virus                                                      |                |       |          |
| 2  | Hepatitis C is spread by sharing needles for drugs                                    |                |       |          |
| 3  | Hepatitis C is mainly spread by unprotected sex                                       |                |       |          |
| 4  | A person can get hepatitis C by getting a tattoo or piercing                          |                |       |          |
| 5  | A person can get hepatitis C by sharing personal material like razors or toothbrushes |                |       |          |
| 6  | To be certain of a hepatitis C infection, a blood test is necessary                   |                |       |          |
| 7  | Hepatitis C damages the liver and can cause liver failure                             |                |       |          |
| 8  | Hepatitis C can lead to liver cancer                                                  |                |       |          |
| 9  | Some people can live many years without symptoms                                      |                |       |          |
| 10 | Part of the people infected with the hepatitis C virus can cure spontaneously         |                |       |          |
| 11 | Drinking a lot of alcohol is a good idea for someone with hepatitis C                 |                |       |          |
| 12 | There is a vaccine to prevent hepatitis C                                             |                |       |          |
| 13 | The treatment for hepatitis C cures everyone who is treated                           |                |       |          |
| 14 | The treatment for hepatitis C currently consists of injections and taking pills       |                |       |          |

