| 15 | The treatment for hepatitis C <del>has to</del> be taken lifelong                     |                |       |          |
| 16 | The treatment for hepatitis C can cause side effects like depression                  |                |       |          |

|    |                                                                                                   |  |  |  |
|----|---------------------------------------------------------------------------------------------------|--|--|--|
| 17 | Substitution treatment can be followed during hepatitis C treatment                               |  |  |  |
| 18 | Once you completed a treatment for hepatitis C, a reinfection is impossible because you're immune |  |  |  |
| 19 | If you have hepatitis C it is not necessary to get a vaccination for hepatitis A or B             |  |  |  |

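### The knowledge scoring rule, as written, gives a mark for endorsing false statements, so the total is distorted and a real gain in knowledge would be attenuated

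*Protocol*

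**What the plan says.** Protocol section 1.10.2 (Section G, knowledge) describes the scale as follows.

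- Length: "Total item in this scale are 19 items".
- Response options: "The answer options will be 'True', 'False' and 'Not sure". Appendix A prints the same three column headings.
- Scoring: "Each answer will be given 1 mark for 'yes' answer and 0 for 'no", with 0 also for not knowing.
- Interpretation: "Total score will range from 0 to 19 and the higher the score reflect higher knowledge of respondent on hepatitis C infection".

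The items are in Appendix A, where knowledge is Section F (Table 3.3 calls it Section D). They mix true statements with others such as "Drinking a lot of alcohol is a good idea for someone with hepatitis C" (item 11), "There is a vaccine to prevent hepatitis C" (item 12) and "Once you completed a treatment for hepatitis C, a reinfection is impossible because you're immune" (item 18). The protocol gives no answer key, no reverse coding and no rule based on correct answers.

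The knowledge score is a secondary outcome (section 1.14.1), the subject of hypothesis H2 (section 1.3) and part of specific objective iv. Section 1.11.2.3 assigns KR-20 to dichotomous items, and the knowledge items become dichotomous once scored 0 or 1.

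**The concern.** The scoring sentence fails in two ways. It names responses that are not on the form, so it cannot be applied as printed. If yes is mapped to True, which is the natural reading, it counts agreement and not correctness. On a true statement the two coincide. On a false statement they are opposite: the error earns 1, and both the correct rejection and Not sure earn 0.

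The total is then compared between arms and over time as a measure of knowledge. Where a participant in the intervention arm learns to reject a false statement they had accepted, the score falls by one mark. Gains on the true items are partly offset by losses on the false ones, so the estimated effect for H2 is too small. KR-20 computed on the same codes would describe agreement with a mixed set of statements, not the consistency of a knowledge scale.

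**Working it through.** **Which items are false.** The protocol has no key, so the number of false items, F, is run over a range.

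- F = 3: items 11, 13 and 15 only. Item 11 (heavy drinking) is false on its face. Item 13 says that treatment cures every patient; section 1.1 claims only a high cure rate. Item 15 says that treatment is for life; Table 3.2 uses a patient who has finished a DAA course.
- F = 7: adds items 3, 12, 18 and 19, taken as false by assumption.
- F = 8: adds item 14 (injections and pills), if it is read against DAA treatment.
- F = 9: adds item 16 (depression as a side effect), on the same reading.

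**The plan's own figure.** Under the literal rule, score = number of True ticks. The minimum is 0 and the maximum is 19 × 1 = 19. The stated range of 0 to 19 reproduces. The stated direction does not, as the next step shows.

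**Scores of three respondents.** With 19 − F true items:

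- Fully informed: True on the true items only. Literal score 19 − F; keyed score 19.
- Ticks True throughout: literal score 19; keyed score 19 − F.
- Wrong on every item: True on the false items only. Literal score F; keyed score 0.

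| F | Informed, literal | True throughout, literal | Wrong on all, literal | Informed, keyed | True throughout, keyed |
|---|---|---|---|---|---|
| 3 | 16 | 19 | 3 | 19 | 16 |
| 7 | 12 | 19 | 7 | 19 | 12 |
| 8 | 11 | 19 | 8 | 19 | 11 |
| 9 | 10 | 19 | 9 | 19 | 10 |

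For every F, the literal maximum of 19 is reached only by endorsing every false statement.

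**Effect on a gain in knowledge.** This is an illustration with assumed figures. Let the chance of a correct answer rise from 0.5 to 0.8 on every item, a gain of 0.3. Let w be the share of non-correct answers that are the wrong option; the rest are Not sure.

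- Keyed gain = 19 × 0.3 = 5.7 marks.
- Literal gain = (19 − F) × 0.3 − F × 0.3 × w.
- F = 7, w = 1: 12 × 0.3 − 7 × 0.3 = 3.6 − 2.1 = 1.5.
- F = 7, w = 0.5: 3.6 − 1.05 = 2.55.

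| F | Keyed gain | Literal gain, w = 1 | Literal gain, w = 0.5 |
|---|---|---|---|
| 3 | 5.7 | 3.9 | 4.35 |
| 7 | 5.7 | 1.5 | 2.55 |
| 8 | 5.7 | 0.9 | 2.1 |
| 9 | 5.7 | 0.3 | 1.65 |

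With F = 7 the score shows 1.5/5.7 = 26% to 2.55/5.7 = 45% of the true gain.

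**When the sign would change.** If the gain is a on true items and b on false items, the literal gain is negative only when w × F × b exceeds (19 − F) × a. With F = 7 and w = 1, b must exceed 12/7 = 1.7 times a. An equal gain on every item shrinks the effect and does not reverse it at any F considered here.

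**The case against.** The strongest defence is that this is a slip of wording. The rule's terms do not match the options in the sentence before it, the next sentence says that a higher score means more knowledge, and the scale is adopted from an earlier study that presumably has its own key. Yes may simply stand for correct. That is plausible, but nothing in the protocol says so, and an analyst who coded the data from this sentence would produce the wrong variable. Even on the charitable reading, items 14 and 16 have no settled answer, because Table 3.2 teaches DAA treatment by contrast with interferon.

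A detailed key may fairly sit in a scoring manual or analysis plan that is not shown. Its absence from the protocol is therefore not the error; the scoring sentence is.

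Three stronger readings are tempting, and the documents do not support them.

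- A reader might infer that misinformed respondents in general outscore informed ones. They do not: with 7 false items, someone wrong on every item scores 7 against 12. The one who outscores is a respondent who endorses enough false statements along with the true ones.
- A reader might infer that the rule cancels or reverses the intervention effect. Reversal needs clearly larger learning on the false items than on the true ones, and nothing in the protocol points to that.
- A reader might infer that the module teaches participants to reject each false statement. Table 3.2 does not list alcohol advice, a hepatitis C vaccine, reinfection, or vaccination against hepatitis A or B.

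The damage is also limited. Knowledge is a secondary outcome, and the answered questionnaires are kept, so scores can be recomputed. The reliability check might expose miskeyed items, although the protocol does not promise that it will.

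**Conclusion.** The scoring sentence is wrong as written, and nothing elsewhere in the protocol repairs it. A fully informed respondent scores between 16 and 10 of 19, for 3 to 9 false items, against 19 for one who ticks True throughout. The direction claimed for the score therefore fails, although the score is distorted and not inverted. A real effect on knowledge would be attenuated: mildly if only 3 items are false (3.9 to 4.35 of 5.7 marks), and severely with 7 (1.5 to 2.55) or more.

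This rests on reading yes as True, on items 3, 12, 18 and 19 being false, which is an assumption, and on the assumed change from 0.5 to 0.8. The failure of the stated direction needs only the three items that can be called false from the protocol or plain sense. The primary outcome, willingness, and the sample size built on it are not affected.

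**What to change.** Replace the scoring sentence in section 1.10.2 with: 1 mark for the correct answer according to a prespecified key, and 0 for an incorrect answer or Not sure. The range stays 0 to 19.

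The expert panel already planned for content validity (section 1.11.2.2) should fix the key for all 19 items before analysis. That includes the items taken as false here by assumption. The panel should settle items 14 and 16, or reword them, in line with the DAA content of the module. Rewording is open only before the questionnaire is used; after that, the printed items need a keyed answer fixed without sight of results by arm. Use the same key for KR-20.

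The cost is one sentence and a 19-line key. No new data are needed as long as the item responses, and not only the totals, are kept so that the score can be derived from them.

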### Section G: Attitude towards hepatitis C infection and treatment

Please indicate your level of agreement with each of the statements below by selecting and marking (✓) at your answer choice in the space provided based on the provided scale.

Question 1: Based on Important scale below

| No | Statement                                                                                             | Not Important | Slightly Important | Moderately Important | Important | Very Important |
|----|-------------------------------------------------------------------------------------------------------|---------------|--------------------|----------------------|-----------|----------------|
| 1  | If you were diagnosed with hepatitis C, how important is it for you to get treatment for hepatitis C? |               |                    |                      |           |                |

Question 2-10: For question 2 to 10, the scale as follow:

|                   |          |         |       |                |
|-------------------|----------|---------|-------|----------------|
| 1                 | 2        | 3       | 4     | 5              |
| Strongly disagree | Disagree | Neutral | Agree | Strongly Agree |

| No | Statement                                                                     | 1 | 2 | 3 | 4 | 5 |
|----|-------------------------------------------------------------------------------|---|---|---|---|---|
| 2  | 'I do not think that I need to take medication for my hepatitis C'.           |   |   |   |   |   |
| 3  | 'I don't believe that I will die from hepatitis C'.                           |   |   |   |   |   |
| 4  | 'Treating my other illnesses is more important than treating my hepatitis C'. |   |   |   |   |   |

|    |                                                                                                       |  |  |  |  |  |
|----|-------------------------------------------------------------------------------------------------------|--|--|--|--|--|
| 5  | 'Treating hepatitis C will make my life better'.                                                      |  |  |  |  |  |
| 6  | 'Hepatitis C does not cause any problems in my body'.                                                 |  |  |  |  |  |
| 7  | I do not think I need treatment for hepatitis C because I can't tell that I have it' (Asymptomatic)   |  |  |  |  |  |

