### Section H: Subjective norms

Please indicate your level of agreement with each of the statements below by **selecting** and **circling** at your answer choice in the space provided based on the provided scale.

|                                                                                                                               |                                                                                                         |
|-------------------------------------------------------------------------------------------------------------------------------|---------------------------------------------------------------------------------------------------------|
| 1. Most people who are important to me think that...                                                                          |                                                                                                         |
| I Should                                                                                                                      | 
 
1
 
2
 
3
 
4
 
5
 
6
 
7
 
 |
|                                                                                                                               | I should not                                                                                            |
| ...get treatment for hepatitis C if I was diagnosed with it.                                                                  |                                                                                                         |
| 2. If I was diagnosed with hepatitis C, it is expected of me that I agree for hepatitis C treatment at the health facilities. |                                                                                                         |
| Strongly disagree                                                                                                             | 
 
1
 
2
 
3
 
4
 
5
 
6
 
7
 
 |
|                                                                                                                               | Strongly agree                                                                                          |

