### Section I: Perceived behavioural control

Please indicate your level of agreement with each of the statements below by **selecting** and **circling** at your answer choice in the space provided based on the provided scale.

|                                                                                                      |
|------------------------------------------------------------------------------------------------------|
| 1. I am confident that I can agree on hepatitis C treatment, if I was diagnosed to have hepatitis C. |
| Strongly disagree   1   2   3   4   5   6   7   Strongly agree                                       |
| 2. For me to agree and go for hepatitis C treatment upon diagnosis is...                             |
| Easy   1   2   3   4   5   6   7   Difficult                                                         |
| 3. The decision to agree and go for hepatitis C treatment upon diagnosis is beyond my control.       |
| Strongly disagree   1   2   3   4   5   6   7   Strongly agree                                       |
| 4. Whether I agree and go for hepatitis C treatment upon diagnosis is entirely up to me              |
| Strongly disagree   1   2   3   4   5   6   7   Strongly agree                                       |

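### The scoring rule for attitude, subjective norm and perceived control conflicts with the direction of the Appendix A items, and no reverse scoring is stated

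*Protocol*

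**What the plan says.** Section 1.10.2 sets the scoring of the three scales. (It letters them H, I and J; in Appendix A they are Sections G, H and I.)

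- **Attitude.** Item 1 uses a five-point importance scale. For items 2 to 10, "the level of agreement of respondent will be rated using 5-point Likert scale ranging from 1 as" strong disagreement to 5 as strong agreement. The total is said to "range from 10 to 50", and "The higher the score indicate the more positive attitude towards hepatitis C infection".
- **Subjective norm.** Four items, all described as seven-point disagree-to-agree ratings, total 4 to 28, higher meaning a more positive norm.
- **Perceived control.** Four items with the same description and range; "The higher the score indicate the more positive perceived behavioral control on willingness for hepatitis C treatment".

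The protocol mentions no recoding for any item.

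Appendix A prints the items. Attitude item 1 asks "how important is it for you to get treatment for hepatitis C", which is favourable, as is item 5. Item 2 reads "I do not think that I need to take medication for my hepatitis C", and items 4, 6, 7 and 8 point the same way. Norm item 1 opens "Most people who are important to me think that" and is anchored from 1 (should be treated) to 7 (should not). Control item 2 is anchored from 1 (easy) to 7 (difficult). Control item 3 is "The decision to agree and go for hepatitis C treatment upon diagnosis is beyond my control", answered from disagree to agree.

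**The concern.** The codes, the totals and the meaning of a high total cannot all hold for these items. If the printed codes are added up, favourable answers raise some items and lower others within the same scale.

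The three totals are secondary outcomes (section 1.14.1). They carry hypotheses H3, H4 and H5 and, with knowledge, specific objective iv. A module that did what it was meant to do could show a fall in attitude, no movement in control and a diluted change in norm. If the conflict is noticed only after unblinded results are seen, the choice of which items to reverse, above all attitude items 9 and 10, would be open to the data.

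**Working it through.** **Inputs.** Codes and ranges come from section 1.10.2, item wording and anchors from Appendix A Sections G, H and I. Section 1.10.2 does not spell out the summing, but its ranges imply it: 10 items × 1 to 5 gives 10 to 50, and 4 items × 1 to 7 gives 4 to 28. Both stated ranges are reproduced. They are the same with or without reversal, so they do not show which was intended.

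**Method.** Sign each item + (agreement or the high anchor is favourable) or − (unfavourable). Sum the printed codes for a respondent who is fully favourable on every item and for one who is fully unfavourable. A favourable shift of d on every item moves the raw total by (number of + items − number of − items) × d.

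**Perceived control** (signs +, −, −, +).
- Fully favourable: 7 + 1 + 1 + 7 = 16. Fully unfavourable: 1 + 7 + 7 + 1 = 16.
- At any consistent level L from 1 to 7: L + (8 − L) + (8 − L) + L = 16.
- Uniform shift: (2 − 2)d = 0, against 4d after reversal.

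**Subjective norm** (signs −, +, +, +).
- Fully favourable: 1 + 7 + 7 + 7 = 22. Fully unfavourable: 7 + 1 + 1 + 1 = 10. After reversal: 28 and 4.
- Uniform shift: (3 − 1)d = 2d, against 4d.

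**Attitude.** Items 1 and 5 are +. Items 2, 4, 6, 7 and 8 are −. Item 3 (not expecting to die of the disease) is − on the natural reading. Items 9 (being treated differently) and 10 (being scared) are arguable, so they are varied.

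| Reading | Fully favourable | Fully unfavourable | Uniform shift |
|---|---|---|---|
| 9 and 10 both − | 2×5 + 8×1 = 18 | 2×1 + 8×5 = 42 | −6d |
| 9 and 10 both neutral (3) | 2×5 + 6×1 + 2×3 = 22 | 2×1 + 6×5 + 2×3 = 38 | −4d |
| 9 and 10 both + | 4×5 + 6×1 = 26 | 4×1 + 6×5 = 34 | −2d |
| 3, 9 and 10 all + | 5×5 + 5×1 = 30 | 5×1 + 5×5 = 30 | 0 |

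With the opposite items reversed and all ten signed, the extremes are 50 and 10, in the stated direction.

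**Illustration on the standardised scale.** The protocol gives no item correlations. A simulation assuming an inter-item correlation of 0.5 and a true shift of 0.5 SD per item gives these standardised differences, raw against reversed: attitude −0.62 against +0.68 (items 9 and 10 both −), norm 0.49 against 0.63, control 0.00 against 0.62.

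**The case against.** **Recoding may be implied.** The protocol is silent on reversal; it does not forbid it. The stated direction holds only if opposite items are recoded, the scales are adopted from published sources whose scoring keys are not at hand, and an item-level key is often left to an analysis plan. A reader might infer that the protocol orders unreversed sums; the text does not support that. The conflict remains, because section 1.10.2 gives one coding direction per scale and describes all norm and control items as disagree-to-agree, which the printed anchors of norm item 1 and control item 2 contradict. This is a rule fixed badly, not a detail left for later.

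**The control score is not literally constant.** A reader might infer from 16 against 16 that every respondent scores 16. Raw totals can still lie anywhere from 4 to 28 when answers are inconsistent. The cancellation is exact only for consistent respondents or for a shift that is equal on every item.

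**The attitude inversion depends on item signs.** This stands. If items 3, 9 and 10 are all read as favourable, the total cancels instead of reversing. On none of the readings tried does it rise with a more favourable attitude.

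**The norm loss is smaller for testing than half.** This also stands. The raw shift is halved, but in the simulation the standardised difference falls by (0.63 − 0.49)/0.63 = 22%.

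**Reliability testing might catch it.** Partly. A reader might also infer that poor alpha would cause good items to be dropped, but section 1.11.2.3 has no deletion rule; item elimination in section 1.11.2.2 rests on the content validity ratio. With standardised items and an assumed absolute correlation of 0.5, alpha = k/(k−1) × (1 − k/V), where V = k + 2 × the sum of signed correlations. On raw codes:
- control: V = 4 + 2(2 − 4)(0.5) = 2, alpha = (4/3)(1 − 4/2) = −1.33;
- norm: V = 4 + 2(3 − 3)(0.5) = 4, alpha = 0;
- attitude, items 9 and 10 both −: V = 10 + 2(29 − 16)(0.5) = 23, alpha = (10/9)(1 − 10/23) = 0.63.

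The first two would be exposed. The attitude scale could pass, since the protocol notes that values down to 0.45 are sometimes accepted.

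**Conclusion.** The concern holds: section 1.10.2 and Appendix A cannot both be followed and give totals with the stated meaning. Scored as written, control does not separate consistent favourable from consistent unfavourable respondents (16 against 16), the raw norm shift is halved (22 against 10 instead of 28 against 4), and attitude runs backwards (between 18 against 42 and 26 against 34) or at best cancels (30 against 30).

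These figures assume consistent answering or a uniform shift, and the attitude figures also rest on the item signs shown. The norm score is weakened, not reversed. Three secondary outcomes and H3 to H5 are affected. A reader might infer that the trial's main result is at risk; it is not, because the primary outcome is a single yes/no question on willingness and the sample size is built on that proportion. The fault can still be corrected from item-level responses, provided the key is fixed before results are seen.

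**What to change.** Add to section 1.10.2 that, before any total is formed and before Cronbach's alpha is computed:

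- attitude items 2, 3, 4, 6, 7 and 8 are recoded as 6 minus the score;
- the direction of attitude items 9 and 10 is decided and written down before results are seen;
- norm item 1 and control items 2 and 3 are recoded as 8 minus the score.

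Correct the description of the norm and control items so that it gives the actual anchors of norm item 1 and control item 2. The cost is a few lines of text and a few recode statements, with no change to conduct or sample size.

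A secondary improvement: clients without hepatitis C are eligible (section 1.7.3.1), yet several attitude items presuppose infection, whereas item 1 is already conditional on diagnosis. If the questionnaire has not been fielded, the cognitive debriefing planned in section 1.11.2 can make these items conditional too, at the price of a small departure from the adopted wording. Section 1.13 is written in the past tense; if data are already collected, rewording is no longer possible but the recoding is.
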